#### Conventional moxibustion group

Patients assigning in conventional moxibustion group will receive fixed acupoint moxibustion. Common practices are similar with the first group. The different manipulation is that the therapists carry out warming moxibustion in traditional acupoint, selecting Xi Yan (EX-LE5) and He Ding (EX-LE2). One point is treated 15minutes a time. Three points are treated by suspended moxibustion at the same time. In the treatment, the therapists make patients the same intensity of local warm sensation as the former group. The sensation of acupoint heat-sensitization phenomenon is not pursued and not avoided in the treatment. Patients receive the treatment two times/day in 1^st ^week (two times/day from 2^nd ^week) for a total of 35 sessions over 30 days.

#### Conventional drug group

Now, intra-articular hyaluronan (HA) or hylan is popular approved for the treatment of KOA [27]. A number of systematic reviews have published positive evidence of efficacy and safety of intra-articular HA for KOA. For example, a recent review proved HA to be an effective, safe, and tolerable treatment for symptomatic KOA [28]. Therefore, this protocol selected Sodium Hyaluronate Injection Intra-articula as the conventional drug. The injection will be used six days a time (2ml) as a total of five times.

### Statistical methods

#### Analysis

We will conduct analysis on an intention-to-treat basis (significance level p < 0.05) using the SAS statistical package program (ver. 9.1.3).The analysis of center effect will be used Cochran-Mantel-Haenszel. Baseline characteristics will be shown as mean ± standard deviation (SD) for continuous data including age, previous duration, and GPCRND-KOA criteria. As for participants' gender, n (%) of male and female in each group will be shown as baseline characteristics. We will conduct between-group comparision in baseline using ANCOVA (analysis of covariance) for continuous data and using Chi-square test or nonparametric test for gender composition considering p < 0.05 as statistically significant.

For outcome measures, the mean differences from baseline values to the end of treatment will be compared using ANCOVA. If any imbalances in baseline characteristics between groups are encountered, we will conduct ANCOVA (analysis of covariance) using these imbalanced variables as covariates and allocated group as fixed factor.

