## Method/design

### Objective

The aim of this study is to investigate the effectiveness of heat-sensitive moxibustion compared with conventional moxibustion or conventional drug treatment (intra-articular Sodium Hyaluronate injection) in patients with moderate to severe KOA in China.

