#### Sample size

We wished to estimate the sample size that would suffice to detect GPCRND-KOA between the heat-sensitive and conventional moxibustion groups. In our previous pilot study, the effective rate in heat-sensitive moxibustion group is 70%, and 50% in the other group. If we apply a two-sided 5% significance level, 95% power the calculated required sample size is approximately 120 participants in each group, according to the following equation. Allowing for a 20% loss to follow up, a total of 144 participants will be required in each group, with 432 participants in total.

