Actually, the aim of this trial contains two parts: "Is moxibustion treatment superior to Sodium Hyaluronate acid injections for KOA? And is heat-sensitive moxibustion superior to conventional moxibustion for KOA?" The latter one is our more interesting goal. According to the current theory of traditional Chinese medicine, moxibustion resulting from the burning of moxa, produces the radiant heat and drug effects to acupoints. This treatment penetrates deeply into the body, restoring the balance and flow of vital energy or life force through acupoints. So the selected of location for manipulating Moxa plays an important role in obtaining good effects. Generally speaking, the location acupoints are fixed along meridians. The conventional moxibustion is promoted for improving general health and treating diseases by stimulating these fixed acupoints. And doctors consider hyperaemia due to local skin vasodilatation as the indicator of moxibustion's effect. However, our clinical experience and observation in the past suggested that stimulating these fixed acupoints might not the best treatment site for moxibustion. In the human being there are two functional states, sensitization state and rest state. When the human body has disease, acupoints on the body surface may be sensitized with various types of sensitization, and acupoint heat-sensitization is a type of acupoint sensitization. acupoint is more than fixed skin site but external sensitive point reflecting the diseases. Therefore, acupoint is variable and depends on the pathological state. Traditional fixed acupints are thought as indicators to searching specific sensitive acupoint. That is, traditional fixed acupints don not consider the state as the key factor to local the acupoint, so the course of fixing the position is imprecisely.

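### The sample size rests on the heat-sensitive versus conventional effective rate, but the stated outcome test is an ANCOVA of mean score change, so the stated power belongs to no clearly planned test

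*Protocol article*

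**What the plan says.** The Sample size section sets out to "detect GPCRND-KOA between the heat-sensitive and conventional moxibustion groups". Its planning values are rates from a pilot study: "the effective rate in heat-sensitive moxibustion group is 70%, and 50% in the other group". It continues "If we apply a two-sided 5% significance level, 95% power" and concludes that "the calculated required sample size is approximately 120 participants in each group". The last step is "Allowing for a 20% loss to follow up, a total of 144 participants will be required in each group, with 432 participants in total".

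The Analysis section gives one method for comparing outcomes between groups: "For outcome measures, the mean differences from baseline values to the end of treatment will be compared using ANCOVA". If baseline variables are imbalanced, they enter as covariates with allocated group as the fixed factor. Chi-square is assigned to the baseline comparison of gender. Cochran-Mantel-Haenszel (CMH) is named for the centre effect and for nothing else.

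The Outcome section defines four response categories from the percentage fall in symptom score together with clinical conditions. It does not say which of them make up the effective rate.

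The Objective is "to investigate the effectiveness of heat-sensitive moxibustion compared with conventional moxibustion or conventional drug treatment". The Discussions section puts two questions, "Is moxibustion treatment superior to Sodium Hyaluronate acid injections for KOA? And is heat-sensitive moxibustion superior to conventional moxibustion for KOA", says that the second interests the investigators more, and later makes the heat-sensitization hypothesis the trial's main aim.

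**The concern.** A power statement belongs to one test of one endpoint in one contrast. Here the number of participants is justified by a binary endpoint in A versus B, while the sentence that governs outcome comparisons describes a test of means. The two can disagree: mean change can differ significantly when the rate does not, and the reverse. The protocol does not say which result decides the trial.

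This is a conflict between two sections of the same document, not a detail that a protocol would leave to a statistical analysis plan. At stake are whether the endpoint that justifies 432 participants has a confirmatory test, and whether the 95% in the Sample size section means anything for the analysis that will be reported.

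**Working it through.** **Inputs** (Sample size section): p_A = 0.70, p_B = 0.50, mean rate 0.60, two-sided α = 0.05 (z = 1.960), power 95% (z = 1.645), stated n = 120 per group, 20% loss, 144 per group, three groups.

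**1. The plan's own figure.** For two proportions with pooled variance under the null:

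n = [1.960·√(2·0.6·0.4) + 1.645·√(0.7·0.3 + 0.5·0.5)]² / 0.20²
= (1.358 + 1.116)² / 0.04 = 153 per group.

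Other two-sided versions at 95% power give 150 (unpooled), 154 (arcsine), 156 (twice the pooled variance) and 163 (continuity-corrected). The stated 120 is not reproduced. At 90% power the unpooled formula gives (1.960 + 1.282)²·0.46/0.04 = 121, so 120 fits about 90% power.

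**2. Power of the rate test at the stated sizes.** Power = Φ{[0.20·√n − 1.358] / 0.678}.

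| n per group | Source | Power |
|---|---|---|
| 115 | 144 × 0.8 | 87.7% |
| 120 | stated requirement | 89.0% |
| 144 | no loss | 93.8% |

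**3. Power of the ANCOVA.** This needs a mean difference and an SD for the score change, and the protocol gives neither. As an assumed range, take a pairwise comparison of means with 120 per group and no gain from covariates. Power = Φ(d·√60 − 1.960), where d is the standardised difference.

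| Assumed d | Power |
|---|---|
| 0.2 | 34% |
| 0.3 | 64% |
| 0.4 | 87% |
| 0.5 | 97% |

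Power of 95% would need d = (1.960 + 1.645)·√(2/120) = 0.465. Nothing in the document ties the score change to that value.

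**4. Where each method is assigned** (Analysis section).

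| Method | Assigned to |
|---|---|
| ANCOVA | outcome measures, as mean change to the end of treatment |
| ANCOVA, chi-square or nonparametric test | baseline comparisons |
| CMH | centre effect |
| Test of the A-versus-B effective rate | not stated |

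**The case against.** The strongest reply is the CMH sentence. CMH works on stratified categorical tables and cannot be applied to ANCOVA means, so a centre-adjusted analysis of the response categories is a plausible reading. This stands in part: a reader might infer that the effective rate is never tested, and the document does not support a statement that strong. But the sentence names neither the effective rate nor A versus B, and the next paragraph gives ANCOVA for outcome measures. The rate test is therefore not clearly planned.

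A second reply is that a test of means may be more powerful than a test of rates. If a normal variable underlies 70% versus 50%, the difference is z(0.70) − z(0.50) = 0.524 SD, and a test of means with 115 per group has about 98% power. That is possible, but response in the Outcome section depends on percentage reduction plus clinical conditions, not on a cut-point of the score change. The figure is an illustration and cannot replace a stated mean difference and SD.

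Third, a reader might infer that the ANCOVA is a single overall three-group test, or that each pair is tested separately at 5%. The Analysis section states neither. If pairs were tested separately, simulation of three independent arm means gives a chance of at least one false claim of 9.0% for A–B and A–C, and 12.2% for all three pairs. If pairs were tested only after a significant overall test, it would be about 5.0%. The higher figures are conditional and not a property of the plan as written. Nor does the Analysis section plan a test at six months; it speaks only of change to the end of treatment.

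Finally, the priority among contrasts is not open: the Sample size and Discussions sections both put A versus B first. The drug contrast is worded differently in the Objective (heat-sensitive moxibustion against drug) and in the Discussions (moxibustion against drug), but the latter is a loose paraphrase and a minor matter.

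**Conclusion.** The concern holds as a mismatch between the Sample size and Analysis sections. The trial is sized on the A-versus-B effective rate, the stated outcome test is an ANCOVA of mean change, and CMH is not assigned to a treatment comparison. The 95% power belongs to no clearly planned test.

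The ANCOVA's power cannot be derived; the 34% to 97% rests wholly on the assumed range of standardised differences. For the rate, power is about 89% at 120 per group and 88% at 115, taking the pilot rates as given and using an unstratified two-proportion test. The conclusion does not depend on how many contrasts are tested or whether the ANCOVA is overall or pairwise.

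**What to change.** In the Analysis section:

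- Name as primary the A-versus-B effective rate at the end of treatment, tested by CMH stratified by centre at two-sided 5%. State which scheduled assessment this is.
- State which Outcome categories count as effective, for example all except ineffective.
- Make the ANCOVA of score change secondary.
- Test A versus C at 5% only if A versus B is significant, following the priority in the Discussions section.

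In the Sample size section, restate the power as about 89% at 120 per group, or about 88% at 115 after 20% loss.

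This is a change of wording, using a method the protocol already names. A versus B keeps its full 5%; the drug comparison becomes confirmatory only if A versus B succeeds. If the investigators want to keep 95% power, the cost is participants: 153 per group, 153/0.8 = 192 after rounding up, and 3 × 192 = 576 in total against 432. If they prefer the ANCOVA as primary, the sample size must be rederived from a stated mean difference and SD.

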### Design

A multi-centre (four centers in China), randomised, subject blinded(group A and B) and assessor blinded, positive controlled trial will be conducted at the Jiangxi Traditional Chinese Medicine Hospital in Nanchang, The first Affiliated Hospital with Anhui University of TCM in Hefei, Jiangsu Traditional Chinese Medicine Hospital in Nanjing, and Shanxi Traditional Chinese Medicine Hospital in Xian. The study will be sequentially conducted as follows: a run-in period of one week prior to randomisation, a treatment period of 30 days (5 sessions per week), and a follow-up period of six months. The total study period will be eight months. At the end of the run-in period, participants will be randomised to the heat-sensitive moxibustion group, the conventional moxibustion group, or the conventional drug treatment group by the central randomization system (Figure 1).This system is provided by China Academy of Chinese Medical Sciences, which adopted the computer telephone integration (CTI) technology to integrate computer, internet and telecom. The random number list will be assign by interactive voice response (IVR) and interactive web response (IWR)[26]. The success of blinding will be assessed at each participant's last visit. Researchers who did not participate in the treatment and who are blinded to the allocation results will perform the outcome assessment

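### Covariates for the score ANCOVA are chosen from observed baseline imbalance instead of being fixed in advance, and Cochran-Mantel-Haenszel is misdescribed as an analysis of centre effect

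*Protocol article*

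**What the plan says.** All the relevant text is in the protocol article, Statistical methods, Analysis, unless noted.

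- Baseline comparison: the variables listed are "continuous data including age, previous duration, and GPCRND-KOA criteria", plus gender. The continuous ones are compared by ANCOVA with no covariate named, and gender is handled "using Chi-square test or nonparametric test for gender composition considering p < 0.05 as statistically significant".
- Outcome comparison: "For outcome measures, the mean differences from baseline values to the end of treatment will be compared using ANCOVA". This carries no condition and names no covariate.
- Covariate rule: "If any imbalances in baseline characteristics between groups are encountered, we will conduct ANCOVA (analysis of covariance) using these imbalanced variables as covariates", with allocated group as the fixed factor. No other rule for choosing covariates is given.
- Centre: "The analysis of center effect will be used Cochran-Mantel-Haenszel". The sentence names neither the response nor the strata. The Design subsection describes "A multi-centre (four centers in China), randomised, subject blinded(group A and B) and assessor blinded, positive controlled trial".
- The Sample size subsection rests on a categorical response, not on the mean score: "the effective rate in heat-sensitive moxibustion group is 70%, and 50% in the other group".

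**The concern.** Under correct randomisation, baseline differences between groups are due to chance. A small baseline p-value does not show that a variable predicts outcome, and a large one does not show that it can be left out. Selecting covariates this way means that nobody can say before the data arrive which model will produce the score result. The wording also leaves discretion, because the trigger for adjustment is not expressly tied to the p < 0.05 criterion.

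The baseline score is the covariate most likely to predict the final score, yet it is not named as a fixed term. Centre is not named in the score model either, although four centres recruit. The one sentence on centre gives Cochran-Mantel-Haenszel a task that it does not perform as usually applied. At stake are the precision of the score comparison, prespecification of its model, and whether the planned centre analysis answers its own question.

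**Working it through.** The plan gives no figure for this point. Its stated sample size ("two-sided 5% significance level, 95% power the calculated required sample size is approximately 120 participants in each group") enters below only as an arm size. The usual formula gives 153 per group for those inputs, but that is a separate matter and nothing here depends on it.

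**1. How often would the rule fire by chance?** The inputs are four listed baseline variables (age, duration, score, gender), each tested at 0.05. Independence is assumed, and the p < 0.05 criterion is taken as the definition of imbalance.

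1 - 0.95^4 = 1 - 0.8145 = 0.185.

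So 18.5% of correctly randomised trials would add at least one covariate. The baseline score itself would be flagged in 5%. This is the chance that the model changes, not a false-positive rate for the treatment comparison.

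**2. What is lost if the unconditional ANCOVA has no baseline covariate?** Let r be the correlation of baseline with final score, with equal variance s² at both times. The document does not give r, so 0.3 to 0.7 is assumed. Variance per patient is 2s²(1 - r) for change and s²(1 - r²) for ANCOVA adjusted for baseline. The ratio is 2(1 - r)/(1 - r²) = 2/(1 + r). The equivalent share of patients lost is 1 - (1 + r)/2.

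| r | variance ratio | equivalent loss |
|---|---|---|
| 0.3 | 2/1.3 = 1.54 | 35% |
| 0.5 | 2/1.5 = 1.33 | 25% |
| 0.7 | 2/1.7 = 1.18 | 15% |

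If instead the baseline standard deviation is k times the final one, the ratio is 1 + (k - r)²/(1 - r²). This equals 2/(1 + r) at k = 1 and falls towards 1 as k falls from 1 towards r. The entry threshold on the score could make k less than 1, so the table is an illustration.

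**3. Does the pre-test distort the error rate or recover the loss?** A simulation used 10,000 runs per scenario, two arms of 120, a standardised effect of 0.36 (assumed), and a pre-test on the baseline score only.

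| r | type I error, test-then-adjust | power, change only | power, test-then-adjust | power, always adjusted |
|---|---|---|---|---|
| 0.3 | 4.4% | 65% | 66% | 82% |
| 0.5 | 4.3% | 79% | 80% | 89% |
| 0.7 | 4.7% | 95% | 95% | 98% |

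Type I error stays at or slightly below 5%. The rule recovers almost none of the lost power, because it fires for the score in only about 1 trial in 20.

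**4. What does Cochran-Mantel-Haenszel do here?** With centre as the stratum, it tests association between treatment and categorical response, adjusted for centre. It yields no centre estimate and no test of whether the treatment effect differs between centres. It could test association between centre and response if centre were the row variable and group the stratum, but the article does not describe that.

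**5. Cost of fixed terms.** Baseline score takes 1 degree of freedom and centre takes 4 - 1 = 3, so 4 in total. A group-by-centre term adds (3 - 1)(4 - 1) = 6.

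**The case against.** The strongest reply is that an ANCOVA of change is prescribed without condition before the imbalance rule appears. ANCOVA needs a covariate, and for a change score the natural one is the baseline value, so the later sentence may only add further variables. This stands in part. A reader might infer that the baseline score is left out, or is adjusted for only when it differs between groups. The text supports no more than that it is not named. The inference is not idle, because the same subsection uses the term ANCOVA for comparing the baseline variables themselves, again without a covariate. The label alone therefore settles nothing. If the baseline score is always included, the loss in step 2 vanishes, but every other covariate still depends on the data.

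On centre, the reply is that a centre-stratified Cochran-Mantel-Haenszel test is a standard adjusted comparison of a categorical response, and the trial is sized on one. That stands too. A reader might infer that centre is ignored, and the document does not support this. What remains is the wrong description and the absence of centre from the score model as stated.

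Finally, a condensed article may leave the covariate list to a fuller plan. That would excuse silence. It does not excuse a stated rule that chooses covariates from the observed data, which a fuller plan would have to reverse.

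**Conclusion.** The point holds as a badly fixed rule that should be changed. The adjustment set for the score analysis depends on observed baseline imbalance. Under four independent tests at 0.05, 18.5% of correctly randomised trials would acquire extra covariates.

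The precision cost is conditional. The variance is 1.18 to 1.54 times that of a baseline-adjusted ANCOVA only if the stated ANCOVA has no baseline covariate, with assumed correlations of 0.7 to 0.3 and equal variances. That cost falls on the score comparison alone and does not touch the effective rate used for the sample size. A reader might also infer that testing first inflates the false-positive rate, but the simulated 4.3% to 4.7% does not support that. The effect of leaving centre out of the score model has not been quantified.

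The centre sentence is a misdescription: it names a centre-adjusted treatment comparison as if it measured centre effect or heterogeneity.

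**What to change.** 1. Delete the baseline significance tests and the rule that adds imbalanced variables. Keep the baseline table as description.
2. State one model for all score analyses, whatever the baseline data show: group, baseline GPCRND-KOA score and centre.
3. Name Cochran-Mantel-Haenszel stratified by centre as the comparison of the effective rate, and drop its description as an analysis of centre effect.
4. Examine heterogeneity between centres separately and as supportive only. Use a group-by-centre term for the score. For the rate, use Breslow-Day tests on pairs of arms, because that test needs a two-by-two table in each centre and the trial has three arms.

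The cost is wording. Baseline score and centre are already recorded. The fixed terms use 4 degrees of freedom, and the supportive interaction uses 6 more, out of 432 planned participants. No new data are needed and clinical conduct does not change.

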#### Data integrity

The integrity of trial data will be monitored by regularly scrutinizing data sheets for omissions and errors. Data will be double-entered and the source of any inconsistencies will be explored and resolved.

#### Sample size

We wished to estimate the sample size that would suffice to detect GPCRND-KOA between the heat-sensitive and conventional moxibustion groups. In our previous pilot study, the effective rate in heat-sensitive moxibustion group is 70%, and 50% in the other group. If we apply a two-sided 5% significance level, 95% power the calculated required sample size is approximately 120 participants in each group, according to the following equation. Allowing for a 20% loss to follow up, a total of 144 participants will be required in each group, with 432 participants in total.

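### The stated 95% power does not fit the stated size: 120 per group for 70% versus 50% at two-sided 5% gives about 89–90%

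*Protocol article*

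**What the plan says.** The protocol article, Statistical methods, Sample size, sizes one pairwise comparison, the two moxibustion groups; it aims to "detect GPCRND-KOA between the heat-sensitive and conventional moxibustion groups". From a pilot study it assumes that "the effective rate in heat-sensitive moxibustion group is 70%, and 50% in the other group". It then states: "If we apply a two-sided 5% significance level, 95% power the calculated required sample size is approximately 120 participants in each group". The allowance for attrition follows: "Allowing for a 20% loss to follow up", "a total of 144 participants will be required in each group, with 432 participants in total".

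The section refers to an equation that is not in the text available to me. The inputs and the answer are all given in words, so the calculation can be checked without it.

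**The concern.** Two event rates, a significance level and a power determine the size of a two-group comparison of proportions. The section gives all of these and the resulting size, so the statement can be checked against itself. A 20-point difference around 60% at two-sided 5% needs roughly 120 per group for 90% power, not 95%.

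This is the only comparison the article sizes. The Discussions section names it as the more interesting of the trial's two questions and makes testing it the main aim. If the power is overstated, the risk of a false negative on that question is understated, and a null result would be read as firmer evidence of no difference than the design supports. The Background also faults earlier trials for their sample sizes, so this trial's own sizing statement should be reproducible.

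**Working it through.** **Inputs, all from the Sample size section:** p1 = 0.70, p2 = 0.50, difference 0.20; two-sided 5% level (z = 1.960); stated power 95% (z = 1.645); equal groups; stated size about 120 evaluable per group; 20% loss.

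Variance terms: p1(1−p1) + p2(1−p2) = 0.21 + 0.25 = 0.46. With the mean rate 0.60, 2 × 0.60 × 0.40 = 0.48.

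**Step 1. Try to reproduce 120 at 95% power.**

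- Unpooled: n = (1.960 + 1.645)² × 0.46 / 0.20² = 149.4, so 150.
- Pooled: n = (1.960 × √0.48 + 1.645 × √0.46)² / 0.20² = 153.
- Other standard forms: 154 (arcsine), 156 (pooled variance under both hypotheses), 163 (continuity-corrected).

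Every form gives 150 to 163, which is 25% to 36% above 120. The stated figure is not reproduced.

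**Step 2. Find the power that 120 does match.** At 90% power (z = 1.2816):

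- Unpooled: n = (1.960 + 1.2816)² × 0.46 / 0.04 = 120.8, so 121.
- Pooled: 124.

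**Step 3. Power at 120 per group, two-sided 5%.**

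- Unpooled: standard error √(0.46/120) = 0.0619; 0.20/0.0619 − 1.960 = 1.27; power 89.8%.
- Pooled: (0.20 − 1.960 × √(0.48/120)) / 0.0619 = 1.23; power 89.0%.
- Exact power of the Pearson chi-square test: 89.4%.
- Continuity-corrected: 86.3%.

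**Step 4. Does the attrition allowance rescue it?** The planned 144 is 120 × 1.2. A 20% loss from 144 leaves 144 × 0.8 = 115.2, about 115.

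| Evaluable per group | Pooled | Unpooled | Exact Pearson |
|---|---|---|---|
| 115 | 87.7% | 88.5% | 87.9% |
| 120 | 89.0% | 89.8% | 89.4% |
| 144 (no loss) | 93.8% | 94.3% | 93.6% |

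No row reaches 95%, and the text ties 95% to 120 before the allowance.

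**Step 5. An illustration that rests on my own assumption.** The Analysis section specifies intention-to-treat but gives no rule for missing responses. If the 20% lost in each arm were counted as ineffective, the rates would be 0.8 × 70% = 56% and 0.8 × 50% = 40%. With 144 per group, power would be about 78%. The finding does not depend on this figure.

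**The case against.** The arithmetic is not in dispute. Five points can be made about how to read it.

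- **Which figure is the slip is not known.** The section shows that rates, level, power and size conflict; it does not show which one is wrong. A one-sided 5% calculation at 95% power gives 125 (unpooled) or 128 (pooled), and one-sided power at 120 is 93.9–94.4%. This stands as a caution about the cause. It does not save the sentence, because the text says two-sided, and two-sided 90% power (120.8 unpooled) fits 120 more closely.
- **The intended evaluable number is 120, not 115.** This is fair as a reading of intent, since 144 was built as 120 × 1.2. But losing 20% of 144 does leave about 115. The effect is small, about 1.3 points of power, and is secondary to the main error.
- **The 78% scenario is not in the plan.** Correct. It is an illustration only, and the finding stands without it.
- **The planned outcome analysis is different.** The Analysis section compares mean changes from baseline by ANCOVA and names no between-group test of the effective rate. The power of that ANCOVA cannot be derived from the article. This is a separate issue. The sizing statement is about proportions and is wrong on its own terms.
- **The consequence is modest.** Power of 88–90% is conventional, enrolment need not change, and neither type I error nor any estimate is affected. This limits the harm but does not make the stated power true. The word approximately cannot cover a gap of 30 or more participants per group.

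**Conclusion.** The concern holds. For 70% versus 50% at two-sided 5%, 120 evaluable per group give 89.0–89.8% power, not 95%. The chance of missing the planned difference is about 10–11% at 120, and about 12% at 115, against the 5% implied. Reaching 95% would take 150 to 153 evaluable per group, or 163 with a continuity correction.

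This rests on the article's own rates and two-sided level, equal groups, a single pairwise comparison and no multiplicity adjustment. It does not depend on the choice of standard formula. It is a certain error in the statement of a key design property and must be fixed, but it does not make the trial inadequate.

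**What to change.** In the Sample size section, check the equation and replace the power statement. Suggested wording: 120 evaluable participants per group give approximately 90% power to detect 70% versus 50% at a two-sided 5% level; if 20% of the 144 enrolled per group are lost, power is about 88%.

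This costs one sentence. The stated power becomes less favourable, and the 144 per group and 432 in total can stay.

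If the sponsor does want 95% power at two-sided 5%, the size must change instead: at least 150 evaluable per group (153 pooled). Allowing for 20% loss, that means enrolling 150/0.8 = 187.5, so 188, to 153/0.8 = 191.25, so 192, per group. If a one-sided test was meant, the sentence must say so, and its power at 120 is about 94%.

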**Methods:**

This study consists of a multi-centre (four centers in China), randomised, controlled trial with three parallel arms (A: heat-sensitive moxibustion; B: conventional moxibustion; C: conventional drug group). The moxibustion locations are different from A and B. Group A selects heat-sensitization acupoint from the region consisting of Yin Lingquan(SP9), Yang Lingquan(GB34), Liang Qiu(ST34), and Xue Hai (SP10). Meanwhile, fixed acupoints are used in group B, that is Xi Yan (EX-LE5) and He Ding (EX-LE2). The conventional drug group treats with intra-articular Sodium Hyaluronate injection. The outcome measures above will be assessed before the treatment, the 30 days of the last moxibustion session and 6 months after the last moxibustion session.

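### The 20% loss allowance is added to 120 rather than divided out: 144 per group less 20% leaves about 115, a minor shortfall against the plan's own target of 120

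*Protocol article*

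**What the plan says.** All the figures stand in the Sample size section of the protocol article. The planning rates come from a pilot study: "the effective rate in heat-sensitive moxibustion group is 70%, and 50% in the other group". The error rates are set by "If we apply a two-sided 5% significance level, 95% power". From these the section concludes that "the calculated required sample size is approximately 120 participants in each group". It then goes on: "Allowing for a 20% loss to follow up, a total of 144 participants will be required in each group, with 432 participants in total".

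The abstract describes a "randomised, controlled trial with three parallel arms", which agrees with 3 × 144 = 432. No other part of the article gives a different loss rate or enrolment figure.

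**The concern.** An allowance for loss should be large enough that the required number remains once the loss has occurred. Here the 20% appears to have been added on top of 120 instead of being treated as the share of enrolled participants who will be lost. If so, the trial misses its own evaluable target at exactly the loss rate it plans for.

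At stake is whether the enrolment figure, on which centres and ethics boards rely, delivers the allowance printed in the same sentence, and whether the loss of information is large enough to matter for the comparison of the two moxibustion groups.

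**Working it through.** **Inputs** (all from Sample size, except the number of arms, which is in the abstract's Methods): required number 120 per group; loss 20%; enrolment 144 per group and 432 in total; rates 70% and 50%; two-sided 5%; stated power 95%; three arms.

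**1. Reproduce the plan's figure.** 120 × (1 + 0.20) = 144, and 144 × 3 = 432. Both match exactly, so 144 comes from adding 20% to 120.

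**2. Inflate for a 20% loss among those enrolled.** n / (1 − d) = 120 / 0.80 = 150 per group; 150 × 3 = 450, which is 18 more than 432. Check: 150 × 0.80 = 120.

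**3. What 144 delivers.** 144 × 0.80 = 115.2, so about 115 evaluable per group, roughly 5 short. The loss that 144 can absorb while still leaving 120 is 1 − 120/144 = 16.7%.

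**4. Effect on power for 70% versus 50%, two-sided 5%.** The difference is 0.20 and the mean rate is 0.60.

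- Unpooled: power = Φ(0.20 / √(0.46/n) − 1.96), where 0.46 = 0.7 × 0.3 + 0.5 × 0.5.
- Pooled: power = Φ((0.20 − 1.96 × √(0.48/n)) / √(0.46/n)), where 0.48 = 2 × 0.6 × 0.4.

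For n = 115, unpooled: √(0.46/115) = 0.0632; 0.20/0.0632 = 3.162; 3.162 − 1.96 = 1.202; Φ = 88.5%.

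| Evaluable per group | Pooled | Unpooled | Exact (chi-square test) |
|---|---|---|---|
| 120 (plan's target) | 89.0% | 89.8% | 89.4% |
| 115 (144 less 20%) | 87.7% | 88.5% | 87.9% |
| Cost of the slip | 1.3 points | 1.3 points | 1.5 points |

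**5. Separate the slip from the gap to 95%.** The number needed for 95% power is 0.46 × (1.960 + 1.645)² / 0.04 = 149.4, so 150 per group by the unpooled formula, and 153 by the pooled one. At 90% power the unpooled formula gives 120.8, so 121. The stated 120 therefore corresponds to about 90% power, not 95%. The 5 to 6 points between 89–90% and 95% are lost before any allowance for dropout is made.

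**The case against.** The strongest reply is that the slip hardly matters. The target is itself only approximate, 20% is a planning guess, the shortfall is 6 enrolled per group (150 − 144, or 4% of 150), and neither the randomisation nor the test is affected and no bias arises. This stands as a judgement of size. It does not rescue the arithmetic: the multiplication was applied to exactly 120 and gave exactly 144, and 144 less 20% does not return 120.

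A second reply is that an intention-to-treat analysis makes the allowance moot. It does not, because the plan itself makes an allowance for loss and so expects loss to cost information.

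A reader might go further and set 88% against the stated 95%, charging the whole difference to the loss allowance. The figures do not support that, since power is already only 89–90% at the full 120.

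A reader might also suppose that lost participants will be counted as not effective, which would lower power much further. The Analysis section names intention-to-treat but states no such rule. Most of that fall would also come from the diluted response rates and little from choosing 144 rather than 150.

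One limit is fair. The Analysis section plans to compare mean changes from baseline by ANCOVA, whereas the power figures here are for two proportions. They test whether the sample size paragraph agrees with itself and do not predict the power of the ANCOVA.

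**Conclusion.** The point holds as a minor error. The enrolment figure does not provide the stated 20% allowance: it provides 16.7%, and a 20% loss leaves about 115 evaluable per group against the plan's own 120. Taken alone this costs about 1.3 to 1.5 points of power. The conclusion assumes equal loss in the groups, the stated rates of 70% and 50%, and a two-sided 5% test of two proportions.

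The larger discrepancy, that 120 per group does not give 95% power, is a separate matter. Correcting the allowance to 150 enrolled would still leave only 120 evaluable and about 89–90% power.

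**What to change.** Keep 432 and replace the sentence on loss to follow-up, for example with:

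> 144 per group allows for 16.7% loss to 120 evaluable (about 89–90% power for 70% versus 50%, two-sided 5%); with 20% loss about 115 remain, giving about 88% power.

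This changes one sentence and needs no extra participants; the price is a less favourable stated figure. Because the wording gives the power at 120, the 95% printed earlier in the same section must be corrected at the same time or the two will conflict.

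If the sponsor prefers to keep the 20% allowance and the target of 120, enrolment becomes 150 per group and 450 in total, 18 more participants. If 95% power is truly intended, the pooled requirement of 153 evaluable gives 153 / 0.80 = 191.25, so 192 per group and 576 in total; changing the inflation step alone will not achieve it.
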